### Participants and eligibility criteria

Women with a diagnosis of EPF between 6 and 14 weeks of gestation. EPF is diagnosed by transvaginal ultrasonography describing:
A crown-rump length ≥ 6 mm and no cardiac activity ORA crown-rump length < 6 mm and no fetal growth at least 1 week later ORA gestational sac with absent embryonic pole for at least 1 week.

A minimum of 1 week of expectant management results in spontaneous complete abortion rates of 50%, and is common practice in the Netherlands [2, 13]. Therefore, women will only be included if a minimum of 1 week of expectant management has been implemented. Women will however be suitable for inclusion immediately if there is an obvious discrepancy of at least 1 week between the crown-rump length and the calendar gestational age. .

Exclusion criteria are age < 16 years, hemodynamic instability, sign of infection, incomplete miscarriage, contra-indications for mifepristone or misoprostol, potential interaction between study-medication and other medication, language barrier or the inability to give informed consent, a known clotting disorder or use of anticoagulants or known risk factors for, or presence of a, cardiovascular disease.

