### Procedures, recruitment, randomisation, and collection of baseline data

Women visiting a hospital in case of EPF are identified and approached to participate in the trial by their treating physician. Trained staff will counsel patients, inform about the aims, methods, reasonable anticipated benefits and potential hazards of the study and hand out the patient information letter. Patients will also be informed about the off-label use of mifepristone and misoprostol. Participation is voluntary and patients may withdraw consent to participate at any time during the study. The investigator can decide to withdraw a subject from the study for urgent medical reasons. Baseline demographics, obstetric and medical history are recorded for all women at the time of randomisation using a case report form. After obtaining written informed consent, randomisation can be performed.

The Clinical Trial Unit of the Radboudumc will coordinate randomisation. Subjects will be randomised in a 1:1 ratio to mifepristone 600 mg oral or placebo using computerised randomisation tables. The randomisation will be conducted using block randomisation and stratified by hospital. After randomisation a unique study number will be assigned corresponding with a study package available in the participating centre containing the blinded study medication. The placebo and mifepristone tablets are identical in appearance so neither the patient nor the physician will know which product is taken. Only the pharmacy will know which medication or placebo the patient has received. Blinding, distribution and labelling of the study medication packages will be coordinated by the clinical trial unit in the Radboudumc (Nijmegen). A sealed list with the label codes will be available there in case of emergencies. These data will be disclosed to the principal investigators only after data on all outcome parameters have been collected for all patients. Regarding misoprostol, the treating physician will prescribe these tablets as usual, disposed by the patients own pharmacy.

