### Statistical issues

#### Sample size calculation

Based on retrospective data in the Radboud University Medical Centre (Nijmegen) that are compatible with data from the literature, we found a complete evacuation rate in the control group in 54 and 67% in the intervention group [21]. We used these rates for the calculation of the sample size with an overall significance level of 5%, α = 0.05, in combination with a power of 80%, β = 0.20. Based on an improvement of complete evacuation rates from 54 to 67%, the trial requires 221 patients in each arm. Considering 3–4% patients lost-to-follow-up, 230 patients per arm have to be included (total 460).

Because of the intended execution of an interim analysis, the sample size will have to be adjusted to maintain a sufficient powered final analysis. This leads to a total number of 464 (1.008*460 = 463,68) required inclusions, 232 per arm.

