#### Data analysis

Data handling will be done anonymized, with the patient code only available to the treating physician and local investigator. Data will initially be analysed according to intention to treat method. The main outcome variable will be assessed by calculating success rates in both groups, relative risks, and 95% confidence intervals. A per protocol analysis will be performed to evaluate the potential of both strategies, taking into account only those cases that were treated according to protocol. Differences between groups will be analysed using the Pearson’s chi-square test or the Fisher’s exact test for categorical variables and the Students t-test for continuous variables. Mann-Whitney U test will be used for non-normally distributed metric variables and univariate and multivariate logistic regression analysis to identify individual factors that are associated with treatment success. Economic analysis will be done according to intention to treat principle. Differences in total costs between the intervention and control group will be calculated.

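### The crude primary comparison is valid and has its stated power, but it may forgo 0 to about 5 points of power by not using baseline factors known before randomisation

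*Protocol article*

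**What the plan says.** The Data analysis section of the protocol article sets out the primary comparison: "The main outcome variable will be assessed by calculating success rates in both groups, relative risks, and 95% confidence intervals". For testing it states: "Differences between groups will be analysed using the Pearson’s chi-square test or the Fisher’s exact test for categorical variables". No covariate is named for either.

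The same section lists a regression with a different aim: "univariate and multivariate logistic regression analysis to identify individual factors that are associated with treatment success".

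Three kinds of baseline information exist before allocation:

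- **Gestational age**, from Participants and eligibility criteria: "Women with a diagnosis of EPF between 6 and 14 weeks of gestation".
- **Diagnostic category**, from the same section. There are two categories based on crown-rump length, and the third is a "gestational sac with absent embryonic pole for at least 1 week".
- **Obstetric history**, from Procedures, recruitment, randomisation, and collection of baseline data: "Baseline demographics, obstetric and medical history are recorded for all women at the time of randomisation using a case report form".

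On allocation, that section says: "The randomisation will be conducted using block randomisation and stratified by hospital". The Sample size calculation section rests on the crude comparison: "Based on an improvement of complete evacuation rates from 54 to 67%, the trial requires 221 patients in each arm".

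**The concern.** The sample size calculation aims at exactly 80% power for a difference of 13 percentage points. Of the 232 women per arm, about 223 to 225 remain after the assumed 3–4% loss, so there is almost no reserve.

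When baseline factors predict a binary outcome, adjusting for them and averaging the model's predictions over the whole trial population gives the same marginal relative risk and risk difference, usually with a narrower interval. It also removes the error that a chance imbalance in a prognostic factor would cause. The plan will already collect such data and fit a logistic model, yet its treatment effect comes from raw proportions. What is at stake is a modest amount of power that may be available at almost no cost.

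**Working it through.** **Step 1: reproduce the plan's figure.** The inputs from Sample size calculation are p1 = 0.54, p2 = 0.67, α = 0.05 and power 80%. Two-sided testing is assumed; the article does not say so, but it reproduces the stated figure. With mean p̄ = 0.605:

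n = [1.960·√(2·0.605·0.395) + 0.842·√(0.54·0.46 + 0.67·0.33)]² / 0.13²

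= [1.960·0.6913 + 0.842·0.6852]² / 0.0169 = 220.8, rounded up to **221 per arm**.

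This matches the article. Power at 221 per arm is 80.0%. At 232·0.96 = 222.7 per arm it is 80.3%, and at 232·0.97 = 225.0 it is 80.7%. The crude analysis therefore delivers the planned power.

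**Step 2: approximate gain from adjustment.** Let R² be the share of outcome variance within arms that the baseline factors explain. Then Var(adjusted) ≈ (1 − R²)·Var(crude). The number needed becomes 221·(1 − R²), and power at 221 per arm equals crude power at 221/(1 − R²). The document gives no value for R², so a range is shown.

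| R² (assumed) | Needed per arm for 80% | Power at 221 per arm | SE ratio |
|---|---|---|---|
| 0 | 221 | 80.0% | 1.000 |
| 0.02 | 217 | 80.8% | 0.990 |
| 0.05 | 210 | 82.0% | 0.975 |
| 0.10 | 199 | 84.0% | 0.949 |
| 0.15 | 188 | 86.0% | 0.922 |

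**Step 3: simulation with three covariates.** There were 3,000 trials per scenario, 221 women per arm and marginal success of 54% versus 67%. Gestational age was a standard normal variable. Failure type and obstetric history were binary, with assumed prevalences of 35% and 55%. The crude risk difference was compared with the standardised difference from a logistic model. The odds ratios are assumptions (per SD for gestational age).

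| Odds ratios (age / type / history) | R² | Crude power | Adjusted power | Variance ratio |
|---|---|---|---|---|
| 1 / 1 / 1 | 0 | 79.4% | 79.5% | 1.01 |
| 1.2 / 1.3 / 1.3 | 0.015 | 80.1% | 80.9% | 1.00 |
| 1.3 / 1.5 / 1.5 | 0.033 | 79.6% | 80.6% | 0.98 |
| 1.5 / 2 / 1.5 | 0.065 | 80.1% | 82.8% | 0.95 |
| 1.7 / 2.5 / 2 | 0.112 | 80.3% | 85.3% | 0.90 |

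Monte Carlo error on each power figure is about 0.7 points. The R² of 0.15 in Step 2 lies beyond the strongest scenario here.

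**Step 4: simulation at the expected evaluable number.** At 223 per arm, with prognostic strength set as a log odds ratio per SD of 0, 0.4, 0.6 and 0.8, crude versus standardised power was 80.1% vs 80.5%, 80.4% vs 82.0%, 79.4% vs 82.9% and 80.3% vs 85.6%. For a single score, the three non-zero strengths correspond to an AUC of about 0.61, 0.66 and 0.70.

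**Step 5: type I error.** In the Step 4 setting it was 4.8% without centre terms, and 5.2% with 20 centre terms and a degrees-of-freedom correction. With 20 centre terms, non-prognostic covariates and a plain robust SE without correction, it was 5.9% against 5.0% for the crude test (Monte Carlo error about 0.35 to 0.4 points). The variance in that setting was about 1% above crude. The number of hospitals is not given, so 20 is an assumption.

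**The case against.** The strongest case against is that nothing in the text is wrong. The crude relative risk is unbiased, the chi-square test is valid, and the sample size was computed for exactly this test. A covariate list is ordinary content for a statistical analysis plan, which is not shown here. All of this stands, and it makes the point an improvement to a stated method rather than the correction of an error.

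A reader might infer that the plan throws precision away, because it seems to expect baseline factors to predict success. The document does not support that. The regression is meant to find such factors, and no section says that gestational age, failure type or obstetric history predicts complete evacuation. In the two weaker prognostic scenarios of Step 3 the gain is 0.8 and 1.0 points, hardly more than simulation error. The gain of 5 points needs odds ratios for which the document offers no evidence.

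A reader might also infer that the planned logistic model could simply replace the crude analysis. It could not. Its coefficients are conditional odds ratios rather than a relative risk, and a model used to search for factors is not a prespecified treatment model.

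Three practical objections also stand and shape the fix:

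- Many centre terms with an uncorrected robust SE can inflate type I error slightly. Step 5 shows that a small-sample correction largely removes this.
- Gestational age is not one defined number. The eligibility section allows a discrepancy of at least one week between crown-rump length and calendar age.
- Neither parity nor the diagnostic category is named as a recorded baseline field. Being needed for eligibility does not prove that the category is coded on the case report form.

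**Conclusion.** The point holds as a possible efficiency gain. The primary analysis is valid and has its stated 80% power, but the treatment comparison leaves out baseline factors that are known before randomisation. If they are prognostic, adjusted and standardised estimation raises power by about 0 to 5 points over the scenarios simulated, with a variance ratio from about 1.0 down to 0.90. If they are not, the loss is negligible.

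These figures rest on two-sided testing, success rates of 54% and 67%, 221 to 223 evaluable women per arm, and assumed prognostic strengths. The article does not show that the analysis is biased, underpowered or at odds with the sample size calculation.

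**What to change.** Before unblinding, prespecify that the primary relative risk and risk difference come from a logistic model standardised over all women in the intention-to-treat population. The specification should fix:

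- **Covariates:** arm, one defined version of gestational age, the diagnostic category of pregnancy failure, and one obstetric-history item confirmed to be on the case report form.
- **Interval:** a robust 95% confidence interval with a small-sample correction.
- **Hospital:** handled in a way that avoids sparse centre terms, for example by pooling small centres under a rule set in advance.
- **Interim:** the same method at the O'Brien-Fleming interim analysis and at the final analysis.
- **Supportive result:** the crude relative risk and its interval, as now planned.

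If the statistical analysis plan already specifies an adjusted primary estimate, the two documents should be aligned.

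The cost is a paragraph of text, a few lines of code, simple imputation of a few missing baseline values, and a check that the diagnostic category is recorded. The sample size of 464 is unchanged.

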### Outcome measures

Primary and secondary outcome measures will be extracted from routine clinical parameters in the patient medical record and patient diary and recorded in a digital case report form. A two-step method will be used to determine treatment success. Ultrasonography will be performed 2 weeks after medical treatment to determine treatment failure defined as a complete gestational sac intrauterine. The definite primary study outcome, complete (success) or incomplete (failure) evacuation, will be determined 6 weeks after treatment [2, 8, 15, 16, 46, 48, 50, 51]. A successful medical treatment will be considered in case of an ultrasonography showing a TED < 15 mm (maximum anterior-posterior diameter, two or 6 weeks after medical treatment) and no evidence of retained products of conception using only the allocated therapy by randomisation.

Secondary outcomes include patient satisfaction, complications, side effects and costs. Other interventions such as urgent surgical curettage, the need for blood transfusion, additional hospital admissions or late interventions such as hysteroscopy will also be reported. Secondary outcome measures are subtracted from the medical record, patient diary and (validated) digital questionnaires. At baseline, day five, and two and 6 weeks after treatment started, questionnaires will be sent by email. To measure the quality of the health status of the patients, two so-called health-related quality of life (HRQoL) instruments will be used: the Short Form 36 health survey and the EuroQol-5D, both available in a Dutch translation. Patient preferences and satisfaction with treatment will be measured using The Client Satisfaction Questionnaire (CSQ-8, digital) two and 6 weeks after treatment. In order to enable a thorough cost-effectiveness analysis patients will also receive the iMTA Productivity Cost Questionnaire (iPCQ) with questions regarding their ability to perform work and with that their productivity loss.

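### SF-36 and EuroQol are measured at baseline, but the stated two-sample tests make no use of the baseline score and so lose some precision

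*Protocol article*

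**What the plan says.** The Outcome measures section of the protocol article sets the questionnaire schedule: "At baseline, day five, and two and 6 weeks after treatment started, questionnaires will be sent by email". It names the health-status instruments as "the Short Form 36 health survey and the EuroQol-5D, both available in a Dutch translation". Satisfaction is measured on a different schedule, with "The Client Satisfaction Questionnaire (CSQ-8, digital) two and 6 weeks after treatment", so that scale has no baseline value.

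The Data analysis section gives one general rule for differences between groups, by type of variable. For continuous variables it is "the Students t-test for continuous variables"; in addition, "Mann-Whitney U test will be used for non-normally distributed metric variables". The only regression named is "univariate and multivariate logistic regression analysis to identify individual factors that are associated with treatment success", which concerns the primary endpoint and not quality of life. The section does not mention SF-36 or EuroQol by name, a baseline covariate, or repeated measurements. It also does not say whether scores are compared as follow-up values or as changes from baseline.

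**The concern.** Women are asked to complete SF-36 and EuroQol before treatment, yet no stated method uses those answers. A woman's score after treatment will usually depend in part on her score before it. A two-sample test on follow-up scores leaves that predictable part in the error term, so the confidence interval is wider than the data require.

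At stake is how sharply the trial can describe any difference in health status between the arms. Whether the treatment works on the primary endpoint is not in question. Because the choice between follow-up, change and adjusted scores is not fixed, it could also be made after the results are seen.

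**Working it through.** **Inputs from the protocol article**
- Sample size calculation: "overall significance level of 5%, α = 0.05, in combination with a power of 80%, β = 0.20", and "improvement of complete evacuation rates from 54 to 67%, the trial requires 221 patients in each arm".
- Outcome measures: SF-36 and EuroQol at baseline and three follow-up times.
- Data analysis: t-test or Mann-Whitney U, with no covariate.

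**Input not in the article**
- r, the correlation between baseline and follow-up scores. It is assumed, and shown from 0.2 to 0.7.

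**1. The article's own figure.** For two proportions, two-sided α = 0.05, 80% power, no continuity correction:

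n = [1.960·√(2·0.605·0.395) + 0.8416·√(0.54·0.46 + 0.67·0.33)]² / 0.13² = (1.355 + 0.577)² / 0.0169 ≈ 220.8, rounded up to 221.

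This matches the stated 221 per arm. It belongs to the binary primary endpoint. The article gives no standard deviation, target difference or power for SF-36 or EuroQol.

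**2. A reference point for a continuous score.** With 221 per arm, an unadjusted t-test on follow-up scores has 80% power at a standardised difference of

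(1.960 + 0.8416)·√(2/221) = 0.267.

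This only sets a common yardstick; it is not a target in the plan.

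**3. Effect of baseline adjustment.** In large samples, with the same r in both arms:
- ANCOVA variance = t-test variance × (1 − r²), so the standard error is multiplied by √(1 − r²).
- Equivalent gain in sample size = 1/(1 − r²) − 1.
- Number per arm for 80% power at 0.267 = 221·(1 − r²), approximately, rounded up.

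| r (assumed) | Variance cut | SE ratio | Equivalent extra women | Power at 0.267 | n per arm for 80% |
|---|---|---|---|---|---|
| 0.2 | 4% | 0.980 | 4% | 81.6% | 213 |
| 0.3 | 9% | 0.954 | 10% | 83.6% | 202 |
| 0.4 | 16% | 0.917 | 19% | 86.4% | 186 |
| 0.5 | 25% | 0.866 | 33% | 89.9% | 166 |
| 0.6 | 36% | 0.800 | 56% | 93.8% | 142 |
| 0.7 | 49% | 0.714 | 96% | 97.5% | 113 |

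**4. If the t-test were meant for change scores.** With equal variances at baseline and follow-up, the standard error relative to the follow-up-score test is √(2(1 − r)): 1.183 at r = 0.3, 1.000 at 0.5 and 0.775 at 0.7. ANCOVA gives 0.954, 0.866 and 0.714. The variance ratio of ANCOVA to change score is (1 − r²)/(2(1 − r)) = (1 + r)/2, which is below 1 for every r below 1. Change scores would therefore use the baseline but still be less precise than ANCOVA. Below r = 0.5 they would be worse than ignoring it.

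These figures are for the t-test. Mann-Whitney U makes no use of the baseline score either, but the r² formula is not exact for it.

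**The case against.** The strongest reply is that the Data analysis section is a generic list of tests in a condensed article. The model for a repeated secondary questionnaire, its covariates and the handling of missing forms usually belong in the statistical analysis plan, which is not shown and may already specify adjustment. This has force and limits how firmly the point can be put. It does not remove it: the article is not silent on continuous outcomes, but states a test, and that test is a poor match for its own schedule.

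Two further replies stand in full:
- **The outcomes are peripheral.** The secondary outcomes listed are satisfaction, complications, side effects and costs. SF-36 and EuroQol appear as instruments, and satisfaction itself has no baseline to adjust for.
- **The gain may be small.** Day 5 falls shortly after misoprostol on days 3 and 4 (Interventions and follow-up), so a low correlation at that time is plausible. At r = 0.2 adjustment gains almost nothing.

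A reader might also infer more than the article supports:
- **That the unadjusted comparison is biased by baseline imbalance.** It is not. A chance imbalance shifts the one realised estimate by an amount that depends on the baseline slope, but it averages out over randomisation and the confidence interval already allows for it.
- **That women are dropped at each time point they miss.** The article does not say how missed questionnaires are handled.
- **That the baseline score is certainly discarded.** This is the plain reading of the stated test, but change scores are not excluded. Step 4 shows that the precision argument survives either way.
- **That baseline forms may be completed after the study tablets.** Nothing in the article suggests this.

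**Conclusion.** The point holds as a minor one about efficiency. For SF-36 and EuroQol the article collects a baseline score and states a comparison that does not adjust for it. The comparison is valid but less precise than it could be, by a factor of 1 − r² in variance. The loss is negligible near r = 0.2 (4%) and material from about r = 0.5 (25%).

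This rests on three assumptions: that the general rule for continuous variables is the one meant for these scores, that the test is run on follow-up values, and that r lies somewhere in the range shown. The first cannot be checked without the analysis plan, and the third cannot be checked from the article. The primary endpoint, the 464 planned inclusions and the CSQ-8 comparison are unaffected.

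**What to change.** For SF-36 and EuroQol only, replace the two-sample test with a baseline-adjusted analysis, fixed before unblinding. Either of these serves:
- ANCOVA at each of day 5, week 2 and week 6, with treatment, baseline score and hospital (the stratification factor); or
- one mixed model over the three follow-up times, with treatment, time, treatment-by-time, baseline score and hospital, allowing for the correlation within each woman.

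Report the adjusted mean difference with its 95% confidence interval at each time. Keep Mann-Whitney U as a sensitivity analysis if residuals are clearly non-normal. Leave CSQ-8 on the stated two-sample test. If the analysis plan already says this, a cross-reference is enough.

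The cost is a few lines of analysis wording. No new data, visits or participants are needed.

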## Abstract

**Background:**

Early pregnancy failure (EPF) is a common complication of pregnancy. If women do not abort spontaneously, they will undergo medical or surgical treatment in order to remove the products of conception from the uterus. Curettage, although highly effective, is associated with a risk of complications; medical treatment with misoprostol is a safe and less expensive alternative. Unfortunately, after 1 week of expectant management in case of EPF, medical treatment with misoprostol has a complete evacuation rate of approximately 50%. Misoprostol treatment results may be improved by pre-treatment with mifepristone; its effectiveness has already been proven for other indications of pregnancy termination.

This study will test the hypothesis that, in EPF, the sequential combination of mifepristone with misoprostol is superior to the use of misoprostol alone in terms of complete evacuation (primary outcome), patient satisfaction, complications, side effects and costs (secondary outcomes).

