### Economic evaluation

A cost-effectiveness analysis will be performed, from a societal perspective. To evaluate which medical treatment strategy is cost-effective, volumes of health care consumed will additionally be measured prospectively alongside the clinical trial together with cost associated with productivity losses. Costs of medical interventions (direct costs) and costs resulting from productivity loss (indirect costs) will be taken into account. Resource uses will be recorded in the case report forms. Standardised unit costs will be calculated using the Dutch manual for costing in economic evaluations.

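### The unrestricted Mann-Whitney rule, read literally, covers total costs, although a rank test does not address the difference in mean cost and can point the other way

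*Protocol article*

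**What the plan says.** The Data analysis section of the protocol article gives a general list of between-group tests. It begins "Differences between groups will be analysed using the Pearson’s chi-square test or the Fisher’s exact test for categorical variables", adds the t-test for continuous variables, and then states that the "Mann-Whitney U test will be used for non-normally distributed metric variables". No variable is named and none is excluded.

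Costs are among the variables that the list could reach. Under Outcome measures: "Secondary outcomes include patient satisfaction, complications, side effects and costs". The Abstract includes costs in the superiority hypothesis.

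The Data analysis section closes with two sentences on economics: "Economic analysis will be done according to intention to treat principle", and "Differences in total costs between the intervention and control group will be calculated". Neither gives a test or an interval. The Economic evaluation section adds "A cost-effectiveness analysis will be performed, from a societal perspective" and defines the components: "Costs of medical interventions (direct costs) and costs resulting from productivity loss (indirect costs) will be taken into account".

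**The concern.** Total cost per woman is a metric variable. It combines direct costs, with extra treatment after some failures, and productivity loss, so it is unlikely to be normal. For such a variable the only inferential rule in the article is the Mann-Whitney test.

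A cost-effectiveness analysis needs the difference in mean cost per woman, because mean cost times the number treated is what a payer or society bears. The Mann-Whitney test asks instead whether a randomly chosen woman in one arm tends to cost more than one in the other. The two questions can have opposite answers when one arm carries a small cost in everyone and the other has more women with a large cost. That is the structure here: the added drug cost falls on all mifepristone patients, and the saving comes from fewer failures.

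At stake is a report in which a calculated cost difference favours mifepristone while the accompanying p-value speaks for the control. The section on interim analysis also has the data safety monitoring board consider the economic evidence, so such a result could enter its advice.

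**Working it through.** **Inputs from the protocol article.** Success 54% (control) and 67% (mifepristone), α = 0.05, power 80%, 3–4% loss, interim factor 1.008 (Sample size calculation). Failure rates are therefore 46% and 33%, a difference of 0.13.

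**Plan's own figure.** The article gives no figure for the cost comparison. Its sample size, which uses the same rates, reproduces. With a two-sided test and pooled variance under the null:

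n = [1.960·√(2·0.605·0.395) + 0.842·√(0.54·0.46 + 0.67·0.33)]² / 0.13² = 220.8, so 221 per arm.

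221/(1 − 0.035) = 229.02, so 230 per arm. 1.008 × 460 = 463.68, so 464 in total, or 232 per arm. With 4% loss, 232 × 0.96 = 222.7, so about 223 per arm are analysed.

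**Direction of the mean and of the ranks.** Let c be the added cost of each mifepristone patient and D the cost of each failure, with 0 < c < D. Both are assumptions, as the article gives no prices.

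- Mean difference (mifepristone minus control) = c − 0.13·D. Mifepristone is cheaper on average whenever c < 0.13·D.
- With no other cost variation, the mifepristone patient is the costlier of a random pair unless she succeeds and the control patient fails. P(costlier) = 0.67·0.54 + 0.33·0.54 + 0.33·0.46 = 0.3618 + 0.1782 + 0.1518 = 0.692. P(cheaper) = 0.67·0.46 = 0.308.

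Example: c = 50 and D = 1500 give a mean difference of 50 − 195 = −145, yet the ranks call mifepristone costlier.

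**Dependence on the other costs.** Simulated trials with 223 per arm, 1000 runs per setting. The last three columns are percentages of runs: mean and ranks opposite in sign, and Mann-Whitney significant (p < 0.05) for mifepristone costlier or cheaper.

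| Assumed other costs | c; D | Opposite signs | Costlier | Cheaper |
|---|---|---|---|---|
| None | 50; 1500 | 98 | 100 | 0 |
| Gamma, SD 50 | 50; 1000 | not recorded | 70–74 | 0 |
| Gamma, SD 100 | 50; 1000 | not recorded | about 5–6 | about 1 |
| Gamma, SD 200 (mean 500 or 1000) | 50; 1000 | 10–11 | 0–0.3 | 17–19 |
| Gamma, SD 300 (mean 500 or 1000) | 50; 1000 | 2–5 | 0–0.1 | 23–28 |
| Gamma, SD 500 (mean 500 or 1000) | 50; 1000 | 4–5 | 0 | 17–25 |
| Lognormal, 60% zeros | 20–50; 1500 | 82–92 | 26–40 | 0–0.1 |
| Lognormal, 30% zeros | 50–100; 1500 | 14–21 | 0.7–2.1 | 4.5–12.2 |
| Lognormal, no zeros | 20–150; 1500 | 6–25 | 0–3.1 | 1.6–41.5 |

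The lognormal costs have median 200 or 500 in the 60%-zeros row and 500 in the other two, with log-scale SD 1 (0.5 in one 60%-zeros run). For c = 50 and D = 1000 the true mean difference is 50 − 130 = −80. In every row mifepristone is truly cheaper on average.

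Reversal needs either little spread in the other costs or many women with none. Once most women have widely varying costs, c is lost in the spread and the two measures usually agree in direction.

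**The case against.** The strongest reply is that the article never says costs will be tested by Mann-Whitney. The test list is generic. Economics then gets two sentences of its own, with its own statement of the analysis set, and a separate section on the economic evaluation. The quantity named is a difference in total costs, which per woman is naturally a difference in means. On that view the rank rule was never meant for costs, and the interval method is a detail that a condensed article leaves to the full protocol or analysis plan.

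Much of this stands. A reader might infer that the plan commits itself to a rank test of costs. The text does not say so; it only fails to exclude it. A reader might also fault the article for giving no incremental cost per complete evacuation or acceptability curve. That is not a defect: a cost-effectiveness analysis is promised, and relating cost to effect is what the term means.

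The size is also open to challenge. Every failure is charged D, whereas the follow-up section allows further treatment to be expectant, medical or surgical. Productivity losses are likely to spread costs well beyond an SD of 50 or 100.

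What remains is that a rule is written, it is unrestricted, and costs fall within its wording. The economic sentences name a contrast without inference, so the rank test is the only stated test for a skewed cost variable.

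**Conclusion.** The point holds as a minor one. Read literally, the Mann-Whitney rule covers total costs, and for costs it answers a different question from the one that the cost-effectiveness analysis poses. That mismatch does not depend on any assumed price.

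Whether the rank test would point the wrong way does depend on assumptions. The 0.692 uses the protocol's rates but supposes little other variation in cost. With widely spread costs and few or no zeros, opposite signs occurred in about 4% to 25% of runs in most scenarios (lowest 2%). With 60% of women at zero productivity cost they occurred in 82% to 92%.

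A reader might infer from the low-spread cases that the trial would probably report mifepristone as significantly costlier when it is cheaper. The documents do not support that: they give no prices, no cost distribution and no share of women without productivity loss. The skewness of costs is itself an assumption, though a likely one. The primary analysis and sample size are unaffected.

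**What to change.** State that the Mann-Whitney rule does not apply to costs. Compare total costs by the difference in arithmetic means between the arms, by intention to treat, with a bootstrap 95% confidence interval.

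This takes a sentence in the analysis plan and a little extra programming. It needs no new data, since resource use and productivity loss are already to be collected.
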